### Oversight and monitoring

#### Research governance and ethics

The trial is administered by Swinburne University of Technology. The study has been approved by Swinburne University Human Research Ethics Committee (SUHREC: 2020/2615), Brigham Young University Human Research Ethics Committee (IRB2020–175). The study received a waiver from University of Manchester as all identifiable data will be controlled and handled by Swinburne University of Technology. The trial is conducted in accordance with the Declaration of Helsinki, Good Clinical Practice guidelines, and the Australian National Statement on Ethical Conduct in Human Research [61]. Major protocol amendments will be submitted to SUHREC for review and approval and detailed in the trial registry. This project is subjected to the online audit tool, project progress review, and end of project review conducted yearly (or earlier if project closes before 12 months). The audit and reviews are conducted by the lead Chief Investigator. Full written informed consent is obtained from participants at the time of the baseline assessment by a member of the research team. A copy of the consent form can be obtained by requesting from the corresponding author.

There are no restrictions of the reporting findings of this trial. Nextdoor Inc., a commercial company, has not reviewed this protocol. Trial results will be published in full in the peer-reviewed literature. Media press releases and stakeholder reports will be released when minimum data is collected (baseline to end of Challenge). There is no intended use of professional writers to convey statistical data and findings.

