Hypothesis 1 (H1): There will be a reduction in loneliness in participants assigned to the Nextdoor KIND Challenge groups compared to the waitlist control group post the 4-week intervention.Hypothesis 2 (H2): There will be a reduction in social isolation in participants assigned to the Nextdoor KIND Challenge groups compared to the waitlist control group post the 4-week intervention.Hypothesis 3 (H3): There will be an improvement in neighbourhood relationship quality and contact outcomes (a) social cohesion and trust, (b) perception that their neighbourhood is improving, (c) higher importance around getting to know their neighbours, (d) more likely to be classed as having a supportive neighbour network than not, (e) have lower neighbourhood conflict, and (f) increased number of neighbourhood contacts, in participants assigned to the Nextdoor KIND Challenge groups compared to the waitlist control group post the 4-week intervention.Hypothesis 4 (H4): There will be an improvement in mental health secondary outcomes, lower (a) depression and (b) social anxiety, (c) stress, and greater (d) quality of life, and (e) positive affect, in participants assigned to the Nextdoor KIND Challenge groups compared to the waitlist control group post the 4-week intervention.

While it is vital to investigate the impact of KIND Challenge post intervention, it is possible for impact on outcomes to be distal; that is indirect effects caused by changes in proximal outcomes. The KIND Challenge aims to reduce loneliness and social isolation, which may lead to later distal impact on other outcomes. Capturing impact at one-month follow-up after the completion of the KIND Challenge enables modelling the maintenance of intervention effects, i.e., are effects sustained at one-month or are sleeper effects present? In addition to understanding whether effects of the intervention are sustained, it is also important to know whether the intervention itself is sustainable. The KIND Challenge acts are positive, engaging, and feasible to the average individuals, and thus designed to be sustainable.
Hypothesis 5 (H5): The Nextdoor KIND Challenge effects noted in H1–4 above will be maintained at one-month follow-up for the participants randomly allocated to KIND Challenge group.Hypothesis 6 (H6): The KIND Challenge is sustainable, participants assigned to the KIND Challenge will continue engaging in acts of kindness at one-month follow-up.

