## Methods

### Trial design

This study is made up of three RCTs and each RCT has two conditions: the KIND Challenge condition and a waitlist control condition. A person enrolled into the KIND Challenge condition will be asked to do acts of kindness at least four times for a duration of 4 weeks and will complete three online assessments. A person enrolled into a waitlist control condition will wait 4 weeks before starting the KIND Challenge and will be required to complete four online assessments. The evaluation of the KIND Challenge will be pre-registered prior to the study launch. Please refer to Fig. 1.

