### Study setting

This trial will be conducted online in three countries (Australia, United States of America, and the United Kingdom). All measures will be administered through the online survey platform Qualtrics.

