### Intervention – Nextdoor KIND challenge

For those receiving the KIND challenge, they will be asked to nominate different activities they could do over a four-week period to address loneliness in their communities. Because the KIND challenge takes place during the COVID-19 pandemic, participants will be asked to adhere to their state or country’s health department safety guidelines when undertaking these activities. We note here the different types of support that can be selected. Participants are also provided an opportunity to specify their activity in a free text box if none of the presented options were relevant.
Emotional support. Show care and concern for a neighbour (e.g., provide a listening ear, cheer up a neighbour who is down, check in on the welfare of a neighbour)Informational support. Provide advice or helpful information to a neighbour (e.g., where to shop, good doctors in the area, potential job opportunities, gardening tips, etc.)Tangible support. Help a neighbour out (e.g., mow their lawn, take in their garbage bins, offer meals, run errands, bring them groceries, etc.)Belonging support. Contribute to a larger neighbourhood effort, action, or activity (e.g., support a neighbourhood business, share your talents/skills with others, neighbourhood clean-up, volunteering, etc.)Companionship support. Have regular contact with a neighbour (e.g., chat across the fence, street or balcony, call on the phone, etc.)Other. Please specify what you did in the textbox.

The KIND Challenge activities have been selected because they are considered to be positive, engaging, and feasible to the average individual, and draw upon the social support literature to tap into emotional support, informational support, tangible support, belonging support [30], and companionship [31–33]. Participants who are enrolled in the Challenge condition will receive an email reminder to complete the activity weekly till the next post-Challenge assessment. After the four-week period, participants in the KIND Challenge condition will be emailed a link to the post challenge survey. One month after this, they will be emailed a link to the final follow up survey. For those in the KIND Challenge group, there will be three surveys over a two-month period if the participant follows the intended structure of the project.

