### Outcomes

Information about a participant’s demographics, mental health, stress, affect, quality of life, and their perception of the level of community engagement and neighbourhood activity within their own neighbourhood will be collected. The questionnaires are standardised tools that measure physical health, mental health, stress, affect, quality of life, and community engagement. We will also include ratings related to behaviour change. This includes questions to measure the actions selected to interact with others, frequency, and duration of those actions (i.e., dose response), and meaningfulness of those actions. See Table 1 for measures and when they are assessed. We further categorised the outcomes into three sections: intervention primary outcome, intervention secondary outcomes, and implementation secondary outcomes (see Fig. 2).

**Table 1 Tab1:** SPIRIT schedule of enrolment, intervention, and assessments of the Nextdoor KIND Challenge

Time point	Baseline T1	Waitlist T2^a^	Post Intervention T3	1 Month Follow Up T4
Enrolment				
Informed consent	X			
Allocation	X			
Assessments				
Demographic form	X			
UCLA-LS3	X	X	X	X
LSNS-18	X	X	X	X
EUROHIS-QOL-8	X	X	X	X
PHQ-8	X	X	X	X
Mini-SPIN	X	X	X	X
PSS-4	X	X	X	X
PANAS	X	X	X	X
CE	X			
SCS	X	X	X	X
Number of Contacts	X	X	X	X
Neighbourhood Perception of Change	X	X	X	X
Neighbourhood Importance	X	X	X	X
Neighbourhood Modified Social Relationship Index	X	X	X	X
Neighbourhood Conflict	X	X	X	X
Neighbourhood interaction since COVID-19	X	X	X	X
Pre-KIND Challenge Neighbourhood Contact and Previous Kindness activity	X	X		
Nextdoor Platform Activity	X	X	X	X
COVID-19 Social Restrictions	X	X	X	X
Challenge Activity Nomination	X^b^	X		
Post-KIND Challenge Activity			X	
Safety			X	
Post-Kind Challenge Overall Impact			X	
Follow-Up KIND Challenge Activity				X

Note. *UCLA-LS3* refers to UCLA Loneliness - Scale Version 3, *LSNS* refers to Lubben Social Network Scale, *EUROHIS-QOL-8* refers to European Health Interview Survey Quality of Life-8, *PHQ 8* refers to Patient Health Questionnaire-8, *Mini-SPIN* refers to Mini-Social Phobia Inventory, *PSS-4* refers to Perceived Stress Scale-4, *PANAS* refers to Positive and Negative Affect Scale, *CE* refers to Community Engagement, *SCS refers to* Social Capital Scale

^a^Only the waitlist group completed T2

^b^Only those randomised into the Challenge condition will be asked to nominate Challenge activities

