### Allocation and blinding

Simple randomization (1:1) will be used as the study is conducted entirely on online questionnaire software Qualtrics. Blinding is not possible in this RCT and there may be recruitment biases that may occur (e.g., those who choose to participate may already be more altruistic and more open to being engaged within research studies).

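### Media release is allowed once end-of-Challenge data are in, with no embargo until the one-month follow-up, so late KIND participants could learn the findings before the self-reports that carry H5 and H6

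*Protocol article*

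**What the plan says.** Under Research governance and ethics, the protocol article states the release rule: "Media press releases and stakeholder reports will be released when minimum data is collected (baseline to end of Challenge". The same paragraph says "There are no restrictions of the reporting findings of this trial". No embargo until the final assessment is stated.

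A further assessment follows the end of the Challenge. For the KIND arm, after the post-Challenge survey, "One month after this, they will be emailed a link to the final follow up survey" (Intervention – Nextdoor KIND challenge). Table 1 lists this as "1 Month Follow Up T4" and repeats loneliness and the secondary scales there. For the other arm, "A person enrolled into a waitlist control condition will wait 4 weeks before starting the KIND Challenge" (Trial design), so its later assessments run about four weeks behind.

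On blinding and mode of assessment: "Blinding is not possible in this RCT" (Allocation and blinding), and "All measures will be administered through the online survey platform Qualtrics" (Study setting).

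H5 states that the effects "will be maintained at one-month follow-up for the participants randomly allocated to KIND Challenge group" (Objectives). H6 asks whether KIND participants are still doing kind acts at that time. Secondary outcomes analysis tests both by within-group ANCOVAs in the KIND arm.

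**The concern.** The release rule is tied to the end of the Challenge and not to the last assessment. Participants know their allocation, rate their own loneliness, mood and neighbour relations, and all belong to one online platform that can contact them by email and push notification (Recruitment and enrolment). Someone who reads that the Challenge worked, or did not, may answer the follow-up survey differently. Publicity about kindness may also prompt further kind acts, or the reporting of them.

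H5 and H6 are the analyses at stake. Because they compare the KIND arm with itself over time, a shift at T4 caused by publicity cannot be separated from real maintenance, decay or a delayed effect. A concurrent control exposed to the same publicity might absorb part of such a shift, but these analyses have none.

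**Working it through.** No figure in the plan bears directly on this point. The check is to build the assessment timeline and see which surveys are outstanding when the trigger is met.

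**Inputs** (Trial design, Intervention, Waitlist condition, Table 1), in weeks from randomisation, with one month taken as 4 weeks. Labels follow Table 1; Secondary outcomes analysis numbers the KIND surveys T1 to T3 instead.

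| Arm | T1 | T2 | T3 (post-intervention) | T4 (one-month follow-up) |
|---|---|---|---|---|
| KIND | 0 | – | 4 | 4 + 4 = 8 |
| Waitlist | 0 | 4 | 4 + 4 = 8 | 8 + 4 = 12 |

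The H1–H4 contrast is KIND T3 against waitlist T2, both at about week 4.

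**Two readings of the trigger, for the last person enrolled in each arm**

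| Trigger | Week | KIND outstanding | Waitlist outstanding |
|---|---|---|---|
| A. KIND arm has finished the Challenge | 4 | T4 | T3, T4 |
| B. Both arms have finished the Challenge | 8 | none (T4 just falling due) | T4 |

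Under A, the last KIND participants have 8 − 4 = 4 weeks before T4. Under B, KIND T4 falls due at the trigger itself. Counting one month as 30 or 31 days instead of 28 would leave it 2 to 3 days later, which changes little. What remains under B is mainly waitlist T4, which H5 and H6 do not use.

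**Who could be exposed under staggered enrolment.** Let L be the week in which the last participant enrols and e the week in which a given KIND participant enrols. Suppose the trigger covers every participant and release is immediate.

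- Under A, release is at L + 4 and KIND T4 is at e + 8. T4 is still outstanding if e + 8 > L + 4, that is, e > L − 4. Only KIND participants enrolled in the last four weeks are exposed, and any delay in preparing the release shortens that window.
- Under B, release is at L + 8. The condition e + 8 > L + 8 requires e > L, which nobody meets.

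The document gives neither the pattern of enrolment nor the time from data to release, so the share of KIND participants exposed under A cannot be calculated. Nor does it give any basis for the size of a publicity effect on the T4 scales.

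**Countries.** Statistical methods treats the countries as three separate trials. Trial status gives one overall period, 6 July 2020 to 31 January 2021. The release rule does not say whether the trigger is applied per country or to all three together. If per country, and if one country runs later than another, a release in the first could reach participants in the second at any assessment they have left, including the one used for H1–H4.

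**The case against.** The strongest reply is that the sentence sets an earliest point and not a date. It does not schedule a release before T4, and it does not itself say that results will be disclosed. Data cleaning, distribution checks and four successive models come before any effect estimate, and these could take up the four-week gap. Under reading B, no stated hypothesis is materially exposed.

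Much of this stands. The text shows that participants could learn the findings before T4, not that they will. Reading B does shrink the problem for H5 and H6 to something small. Two things do not answer the point. The release sentence directly follows those on reporting findings and publishing results, so taking it to cover findings is fair. And nothing in the article selects reading B or imposes a delay.

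Three stronger inferences are tempting, and the document does not support them:

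- **That the primary comparison is put at risk by an early look.** On the ordinary reading, a country's data from baseline to end of Challenge are complete at the trigger, so its own H1–H4 comparison is already collected. No interim analysis is planned.
- **That the countries will contaminate each other.** This depends on a per-country trigger and on differing timetables, neither of which is stated.
- **That the harm can be scaled against the minimum detectable effect of .14 in Sample size.** That figure is for the between-arm intention-to-treat effect. It is the wrong yardstick for within-arm analyses, and any publicity shift set against it would be invented.

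**Conclusion.** The point holds in a limited form. The article states a release rule that omits the one-month follow-up, and it adds no embargo. If the trigger is the KIND arm's T3, KIND participants enrolled in roughly the last four weeks could learn the findings before T4, which could bias H5 and H6. If both arms must first finish the Challenge, the exposure falls mainly on waitlist T4 and the effect on H5 and H6 is small. A country's own H1–H4 comparison is unaffected once its end-of-Challenge data are complete; exposure of another country's participants is conditional on a per-country trigger.

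This rests on one month being about four weeks, on surveys being completed when due, and on the released reports disclosing findings. Neither the proportion exposed nor the bias can be quantified from the document. The case for changing the text is that the safeguard is cheap, not that harm has been shown.

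**What to change.** Replace the release sentence with:

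> Media press releases and stakeholder reports that disclose trial findings will be released only after the last one-month follow-up (T4) assessment has been collected in every country still collecting data.

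This removes the need to choose between the two readings of the trigger and covers the cross-country case. Publicity that discloses no findings is untouched. No analysis, sample size or participant procedure changes.

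The cost is delay. Counting from the week-4 end of Challenge of the last participants enrolled, KIND T4 comes 8 − 4 = 4 weeks later and waitlist T4 12 − 4 = 8 weeks later, so about one to two months. It would be longer if one country finishes after the others.

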#### Serious adverse events

An adverse event within this study is defined as participants reporting more than discomfort (e.g., distress) over a particular aspect of the current study. Due to the nature of the survey questions as well as the nature of the KIND Challenge (i.e., doing acts of kindness), we anticipate minimal risk to participants. Participants will be asked questions about their mental health but are not coerced into answering questions and can skip a question or close the survey at any time. Participants will be encouraged to seek counselling and support services if they feel they need someone to talk to. Participants will also have to the research team and ethics officer’s details should they choose to discuss any potential risk issue. The number for each country’s crisis service will also be provided in the participant information and consent form as an additional safety measure. If a participant opts for direct assistance and permits us to contact, we can debrief the participant and refer appropriate country specific services.

#### Trial management committee

A trial management committee will involve the named authors on this protocol as well as an independent academic not associated with the project. The project will be coordinated by the chief investigator who will also collaborate with senior co-investigators with regards to overseeing the trial. The chief investigator will ensure that each member of the trial management committee will be responsible for ensuring the safety of the participants and the quality of the trial is not compromised.

## Discussion

Loneliness is an emerging issue in our communities and while solutions to loneliness are often widely implemented, these are rarely evaluated [3]. One strategy that holds the potential to improve relationship quality is doing acts of kindness. The aim of this study is to assess the acceptability, feasibility, and effectiveness of an evidence-based strategy, specifically acts of kindness, on loneliness and social isolation. While positive psychology strategies have been thought to be useful in reducing loneliness, these strategies are not evaluated within our community. This study will be the first study of its kind to evaluate the impact of kindness on loneliness in communities across three countries. It is therefore crucial that we evaluate the effectiveness of these simple positive actions on loneliness and social isolation in our community.

An additional point to note is that this study is conducted during the COVID-19 pandemic. The COVID-19 pandemic has highlighted the social needs of vulnerable people in our community, and it is more important than ever to assist our community [62]. Loneliness and social isolation are consequences of this global public health crisis. Countries such as the UK, USA, and Australia who are participating in this research are undergoing different social restrictions which we have to statistically control for. Furthermore, acts of kindness typically conducted in person will have to be performed within safe and flexible ways. Participants should first and foremost adhere to their government or state health regulations to ensure safety of the participant and those who they interact with. This will be emphasised through the study. Despite the COVID-19 pandemic challenges posed to the study, there is still flexibility around how participants show acts of kindness safely and have given recommendations on how they can do them safely (e.g., calling a neighbour). Promoting community cohesion during this public health crisis is more crucial than ever and if effective, simple actions such as acts of kindness should be encourage in order to promote community cohesion, health and wellbeing.

### Trial status

Six months from 6 July 2020 to 31st January 2021.

## Data Availability

The datasets during the current study are available from the corresponding author on reasonable request and only by approval from the funder. Should data be released, all identifying data will be removed in order to adhere to confidentiality guidelines stipulated in this trial.

## Abbreviations

PPA: Positive psychology activities
RCT: Randomised controlled trial
UCLA-LS: UCLA Loneliness Scale - Version 3
LSNS: Lubben Social Network Scale
SRI: Social Relationship Index
PHQ: Patient Health Questionnaire-8
Mini-SPIN: Mini-Social Phobia Inventory
EUROHIS-QOL-8: European Health Interview Survey-Quality of Life – 8-Item Index
PANAS-PA: The Positive and Negative Affect Schedule – SF
PSS-4: Perceived Stress Scale-4
MDES: Minimum detectable effect size
ITT: Intention-to-treat
MAR: Missing at random
FIML: Full information maximum likelihood
SUHREC: Swinburne University Human Research Ethics Committee
